**Questionnaires**						
*Patient*						
CCQ	X					
MRC dyspnea	X					
SGRQ	X	X	X	X	X	
McGill QOL	X	X	X	X	X	
HADS	X	X	X	X	X	
Illness understanding	X	X	X	X	X	
Demographic questionnaire	X					
*Informal caregiver*						
SPPIC	X	X	X	X	X	
HADS	X	X	X	X	X	
Illness understanding	X	X	X	X	X	
Demographic questionnaire	X					
*Lung specialist*						
CRF	X					
**Medical files**						
Number of hospitalisations of unexpected hospital admissions for AECOPD						X
Number of days of unexpected hospital admissions for AECOPD						X
Number of hospitalisations of unexpected ICU admissions for AECOPD						X
Number of days of unexpected ICU admissions for AECOPD						X
Are the choices of ACP documented in the medical file at baseline? (when yes/when no)						X
Are the choices of ACP documented in the medical file after one year or at time of death? (when yes/when no)						X
Did the patient die within one year after inclusion? (when yes/when no)						X
Date of death						X
Place of death (ICU/hospital/hospice/nursing home/at home)						X
Is preferred place of death known? (when yes/when no)						X
Has this wish come true? (when yes/when no)						X
Primary cause of death (pulmonary insufficiency/other cause)						X
Secondary cause of death (pulmonary insufficiency/other cause)						X
Did the patient have an unexpected hospital readmission for AECOPD within 8 weeks? (when yes/when no)						X
Date of first unexpected hospital readmission for AECOPD.						X

B = baseline; m = month; R = retrospectively.

### Instrument selection

#### Questionnaires used as indicator

In order to be able to decide whether or not to start proactive palliative care, questionnaires used as indicator will be filled out by the patient.

We will use the CCQ day version to measure health status of patients. The CCQ is a questionnaire for self-administration specially developed to measure health status in patients with COPD and is valid, responsive, and reliable [42,43]. The CCQ consists of 10 questions rated on a seven point Likert scale. Higher scores represent a worse health status. Questions are divided into three domains: symptoms (4 questions), functional status (4 questions), and mental state (2 questions).

The MRC dyspnea scale has been in use for many years for grading the effect of breathlessness on daily activities [44]. The MRC dyspnea scale consists of 5 questions and provides a simple and valid method of categorizing patients in terms of their disability due to COPD [44]. The patient’s dyspnea is rated from 1–5 in terms of severity, with the higher the grade, the more severe the dyspnea. During the study MRC dyspnea will be measured by asking about the circumstances two weeks before hospital admission.

#### Questionnaires used as outcome measures

##### Patient questionnaires

The SGRQ is a specific quality of life questionnaire for obstructive respiratory diseases [36]. It consists of 50 questions from which a total score is calculated. It is divided into three subscales: symptoms (8 items related to patients’ recollection of their symptoms), activities (16 items on physical activities which are caused or limited by dyspnea), and impacts (26 items on the social and physiologic effects of the disease). The final score obtained ranges from zero to 100. A higher score indicates a lower quality of life. A score change of 4 points or more is considered significant in the quality of life of the patient [45]. The SGRQ is a reliable and valid measure of the quality of life in patients with COPD [46].

The McGill QOL is designed to assess quality of life in patients with a life-threatening illness [37]. The questionnaire consists of 16 items with an 11-point scale (0–10) with appropriate anchors. It includes 5 domains: physical symptoms, physical well-being, psychological well-being, existential issues and support. The mean of all 5 domains is presented as McGill QOL total score. The acceptability, internal consistency, reliability and validity of the McGill QOL have been assessed in patients receiving palliative care [47].

The HADS will be used to assess psychological wellbeing in patients. The HADS is a self-assessment 14-item questionnaire. It has two 7-item subscales assessing depression and anxiety in the preceding week. The format consists of four answering categories (0–3) that quantify the degree to which a particular emotion is experienced by the patient. The score on each subscale ranges from 0 to 21 and a score larger than 11 is considered to be consistent with definitive depression and anxiety. A score less than 7 is normal and a score of 8–10 is considered borderline for depression and anxiety [38].

Patients with COPD tend to be poorly informed about the long-term prognosis of COPD and what to expect toward the end of life [48]. They may not realize that COPD is incurable and fatal. They also may not always attribute repeated exacerbations to advancing disease but instead seeing them as temporary setbacks caused by activities, environmental factors, faltering self-management, or infection. Toward the end of life this lack of understanding may impair quality of life [2,49]. There are no validated tools to assess illness understanding in patients with COPD. Therefore, we adapted an illness understanding questionnaire used in studies of patients with advanced cancer [50]. The questionnaire consists of 4 self-report items which can be answered by yes or no.

Patients will be asked in a demographic questionnaire to indicate their sex, age, marital status, education, smoking history, living situation, name of main informal caregiver and kind of relationship with their main informal caregiver.

##### Informal caregiver questionnaires

The Self-Perceived Pressure from Informal Care questionnaire (SPPIC) is a non-disease specific instrument assessing the demands of the informal caregiver situation [39]. This instrument consists of nine statements that form a hierarchical scale that varies from less to more pressure. The statements are all related to the subjective perception of the informal caregiver. It is a validated and easy to use instrument since completing it takes less than 5 minutes.

The HADS (see patient questionnaires) will also be used in informal caregivers to assess psychological wellbeing. An adapted version of the illness understanding questionnaire for patients will be used for the informal caregivers as well. Finally, informal caregivers will be asked to indicate their sex, age and education in a demographic questionnaire.

### Sample size calculation

The primary outcome in the intervention study is the quality of life of the patients measured with the SGRQ. More specifically the change in SGRQ three month after inclusion is the variable of interest. Koff et al. [51] published a difference in change of 9 between the two groups (standard care, standard care with proactive palliative care) with a common standard deviation of the change of 16. Then 64 patients would be needed in each group to obtain a power of 80% (two-sided *t*-test, alpha = 0.05). To adjust for the clustering at hospital level (ICC = 0.01, three hospitals per arm) and to allow for an additional loss to follow up of 10% a total of 86 patients are needed in each arm. This means that in each hospital 29 patients with an AECOPD are needed who have a poor prognosis according to our criteria. We expect to have to include between 60 and 90 patients with an AECOPD in each hospital to get sufficient patients that meet at least 2 criteria of the set of indicators.

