Unfortunately, no research data is available on the beneficial effects of a multidisciplinary approach to proactive palliative care for patients with COPD in terms of reducing the healthcare utilization (for example, hospital readmission) or improving quality of life. However, in a study in male patients predominantly diagnosed with cancer but also with cardiovascular and pulmonary diseases, the benefits of palliative care provision appeared effective compared with usual care [33]. Patients receiving palliative care were less likely to be admitted to the ICU during hospitalization, had lower inpatient cost per day and received better medical care provision compared to usual care patients. Hence proactive palliative care may avoid admission to the ICU for patients with COPD and may help to reduce health care costs. More research data is available concerning the beneficial effects of an early introduction of palliative care for patients with cancer. In a recent study [34] the effect of introducing early palliative care among patients diagnosed with metastatic non-small-cell lung cancer was examined in a randomized controlled trial (RCT). As compared to patients receiving standard care, patients receiving early palliative care had a better quality of life, less depressive symptoms, less aggressive care at the end of life and longer survival.

In the present study the effects of proactive palliative care performed by a specialized palliative care team for patients with COPD on the wellbeing of these patients and their informal caregivers will be examined. We hypothesize that proactive palliative care for patients with COPD will: increase the quality of life of these patients, decrease the number and length of acute hospital admissions and ICU admissions, prolong survival of these patients, decrease the number of patients that die in the ICU, and decrease the level of overburdening of their informal caregivers.

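### The 64 patients per group do not follow from a difference of 9, an SD of 16 and 80% power; those inputs need 51, so at least one printed figure is misstated

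*Protocol article*

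**What the plan says.** The section "Sample size calculation" of the protocol article bases the intervention study on the change in SGRQ three months after inclusion. It takes from a cited publication a "difference in change of 9 between the two groups", naming the groups as standard care and standard care with proactive palliative care, "with a common standard deviation of the change of 16". From these it concludes: "Then 64 patients would be needed in each group to obtain a power of 80% (two-sided *t*-test, alpha = 0.05").

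Only after that does it adjust for clustering ("ICC = 0.01, three hospitals per arm") and for 10% loss to follow-up. This gives 86 patients per arm and 29 per hospital. The 60 to 90 inclusions expected per hospital are set so as to yield those 29.

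On the evidence for such an effect, the Background section on the organization of proactive palliative care says: "Unfortunately, no research data is available on the beneficial effects of a multidisciplinary approach to proactive palliative care for patients with COPD". That sentence goes on to name healthcare utilization and quality of life.

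**The concern.** Every input to the first step is printed, and so is its result, but the result is not what the inputs give. The paragraph offers no other difference, SD, power or significance level that would lead to 64.

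This is the sample size for the primary outcome of the intervention study, and the per-hospital target is built on it. As printed, a reader has two descriptions of the same trial: one sized for 9 points with SD 16 at more than the stated power, and one sized for a somewhat smaller standardised effect at the stated power. A report that quotes this paragraph will carry the mismatch forward.

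A smaller matter concerns the source of the 9 points. It is presented as a published contrast between care with and without proactive palliative care, while the Background says evidence on the multidisciplinary form of that care is lacking. The two statements sit uneasily together.

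**Working it through.** **Inputs, all from "Sample size calculation":** difference in change δ = 9; SD of the change σ = 16; power 80%; two-sided t-test, α = 0.05; equal groups; ICC = 0.01; three hospitals per arm; 10% loss.

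**Step 1: the first figure.** The standardised difference is d = 9/16 = 0.5625.

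- Normal approximation: n = 2(1.960 + 0.842)²/d² = 2 × 7.849/0.3164 = 49.6, so 50 per group.
- Exact two-sample t-test (noncentral t): n = 50.6, so 51 per group.
- The protocol states 64, which is not reproduced.
- Power of the t-test with 64 per group at d = 0.5625: 88.4%.

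**Step 2: can another reading give 64?** At δ = 9 and σ = 16, unless stated otherwise:

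| Variant | n per group |
|---|---|
| One-sided, 80% power | 40 |
| Two-sided, 85% power | 58 |
| Two-sided, 88% power | 64 |
| Two-sided, 90% power | 68 |
| Two-sided α = 0.025, 80% power | 62 |
| Two-sided α = 0.01, 80% power | 76 |
| δ between 8.5 and 9.5, σ between 15.5 and 16.5, 80% power | 43 to 61 |

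Only 88% power gives 64, and that contradicts the stated 80%. Rounding of the inputs does not reach it.

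**Step 3: what 64 corresponds to.** For d = 0.5 the exact t-test needs 63.8, so 64 per group, with 80.1% power. That is a difference of 8 with SD 16, or 9 with SD 18. With δ = 9, the SD that makes 64 give 80% power is 18.03. With σ = 16, the difference is 7.99.

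**Step 4: the later steps, starting from 64.**

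- Patients per hospital: 64/3 = 21.33.
- Design effect: 1 + (21.33 − 1) × 0.01 = 1.2033.
- 64 × 1.2033 = 77.0; 77.0/0.9 = 85.6, so 86 per arm.
- 86/3 = 28.7, so 29 per hospital.

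Both printed figures are reproduced. This also shows that 64 is neither a typing slip nor a number already inflated for clustering or loss.

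**Step 5: the same steps, starting from 51.**

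- Patients per hospital: 51/3 = 17.
- Design effect: 1 + 16 × 0.01 = 1.16.
- 51 × 1.16 = 59.2; 59.2/0.9 = 65.7, so 66 per arm and 22 per hospital.

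**Step 6: power of the printed target, by the protocol's patient-level method.**

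- 86 × 0.9 = 77.4 per arm remain after loss, or 25.8 per hospital.
- Design effect: 1 + 24.8 × 0.01 = 1.248.
- Effective n per arm: 77.4/1.248 = 62.0.
- Power at d = 0.5625: 87.4%. Power at d = 0.5: 78.9%.

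**The case against.** The strongest reply is that nothing of substance turns on this. On the printed inputs the error is conservative: the trial asks for more patients than it needs and has about 87% power after clustering and loss. If a standardised difference of 0.5 was intended, the same 86 per arm gives about 79%, which is close to nominal. Only one link in the calculation is broken. This stands, and it is why the point is moderate and changes no patient numbers. It does not remove the contradiction, since all the figures sit in one intact paragraph and cannot all be right.

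Several stronger readings are tempting, and the document does not support them.

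- *The trial is underpowered because of this error.* On the stated inputs it is not.
- *The target effect cannot be known.* The simplest candidates are close together: 9 with SD 16 at about 88% power, or a standardised difference of 0.5 at 80%. At SD 16 they differ by one SGRQ point.
- *The 9 points come from a different kind of intervention.* The cited study is not at hand, so what it compared cannot be asserted. The parenthesis naming the two groups may simply label this trial's arms. The Background sentence concerns a multidisciplinary approach, which the sample size section does not attribute to the cited study. The two passages are in tension, not in strict contradiction.
- *The surplus of 86 over 66 covers the small number of hospitals.* If the test had only 4 cluster-level degrees of freedom (six hospitals less two), 86 per arm at 9/16 would give about 65% power. That is a separate question, and this arithmetic is no defence of 86.

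**Conclusion.** The point holds. A difference of 9 with SD 16 needs 51 patients per group for 80% power, not 64, and 64 per group gives 88%. At least one of the difference, SD, power or n is misprinted, and the document does not show which. The 86 per arm and 29 per hospital follow correctly from 64; from 51 they would be 66 and 22, a gap of 20 patients per arm.

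The figures of 87% and 79% for the printed target assume ICC 0.01, 10% loss, equal hospital sizes and patient-level degrees of freedom, as in the protocol's own method. This is an internal inconsistency in the primary sample size, conservative on the stated inputs and of moderate severity. The origin of the 9 points is a supporting matter that needs clarification; the arithmetic does not depend on it.

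**What to change.** Restate the paragraph in "Sample size calculation" so that the inputs reproduce the output, in one of two ways:

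- If 64 came from other inputs, print the ones used, for example a difference of 8 with SD 16 or a difference of 9 with SD 18.
- If 9 and 16 are right, either restate the power (about 88% before and 87% after clustering and loss) or restate the n (51 per group, giving 66 per arm by the same steps).

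In the same edit, say what the cited study compared and whether the 9 points were observed for that contrast or are a planning assumption for this one. Then reconcile the wording with the Background statement on missing data.

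The cost is a text correction and a check of the original calculation. Unless the authors choose to restate the n, patient numbers do not change.

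### The sample size inflates for clustering but ignores that six hospitals leave only 4 degrees of freedom: power at the stated inputs is about 65%, not 80%

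*Protocol article*

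**What the plan says.** Under Study design, the article describes a controlled trial with hospital as the cluster, three hospitals per condition. Under Randomization, it says that hospitals enter the intervention condition because they have a specialized palliative care team.

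Under Sample size calculation, the basis is an earlier study that "published a difference in change of 9 between the two groups"; the SD of the change is taken as 16. From this the article concludes: "Then 64 patients would be needed in each group to obtain a power of 80" percent. The test assumed there is two-sided at the 5% level. The clustering step is introduced as "To adjust for the clustering at hospital level (ICC = 0.01, three hospitals per arm"). Once a 10% dropout allowance is included as well, the figure becomes 86 per arm. The section then states: "This means that in each hospital 29 patients with an AECOPD are needed who have a poor prognosis according to our criteria".

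Under Statistical analysis (intervention study), the change in SGRQ at 3 months is compared between groups with what the article calls a paired t-test. No hospital term is named. Linear mixed models adjusted for baseline are named for SGRQ over follow-up, also without a stated hospital term.

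Under Patient questionnaires, the relevant change on the SGRQ is given: "A score change of 4 points or more is considered significant in the quality of life of the patient".

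**The concern.** A design effect corrects the variance of the group difference for clustering. It does not correct the reference distribution. When whole hospitals carry the condition, the error for the condition effect is estimated from differences between hospitals within a condition. Three hospitals per condition give 2 × (3 − 1) = 4 degrees of freedom for that estimate. With hundreds of clusters the distinction does not matter; with six it dominates.

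The 80% is therefore a claim about a test that treats patients as independent replicates of the condition once the variance has been inflated. The section itself accepts that clustering must be adjusted for. If the adjustment is incomplete, the trial has a materially greater chance of missing the effect it was sized for, and its interval will be wide relative to the 4-point relevant change.

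**Working it through.** **Inputs**, all from Sample size calculation: difference 9; SD of change 16; two-sided alpha 0.05; ICC 0.01; three hospitals per arm; 10% loss; 86 per arm. The 4 df are not written in the article; they are the standard between-cluster df (hospitals minus conditions) for its design.

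**1. The plan's own figures.**
- Exact two-sample t-test, 9/16, 80% power: 51 per group (50 by the normal approximation), not 64. With 64 per group, power at 9/16 is 88%. A difference of 8 with SD 16, a standardised difference of 0.5, gives exactly 64.
- From 64 to 86: cluster size 64/3 = 21.3; design effect 1 + 20.33 × 0.01 = 1.203; 64 × 1.203 = 77.0; 77.0/0.9 = 85.6, rounded up to 86. This reproduces, and contains no small-sample term.

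**2. Standard error at the planned size.**
- Analysed per arm: 86 × 0.9 = 77.4, or 25.8 per hospital.
- Design effect: 1 + 24.8 × 0.01 = 1.248.
- SE = 16 × √(2 × 1.248/77.4) = 2.87.
- Noncentrality: 9/2.87 = 3.13.

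**3. Power for 9 points.**
- Same SE with patient-level df: about 88%.
- Noncentral t on 4 df, critical value 2.776: **65.5%**. Simulation of a t-test on hospital means with 26 patients per hospital (40,000 runs) gave 65.8%, with type I error 5.1%.

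**4. Sensitivity on 4 df.** The ICCs other than 0.01 are assumed.

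| Setting | Power |
|---|---|
| ICC 0.01, no loss (86 analysed per arm) | 68.9% |
| ICC 0, 10% loss | 74.5% |
| ICC 0.02, 10% loss | 58.1% |
| ICC 0.05, 10% loss | 43.1% |
| Difference 8, SD 16, ICC 0.01, 10% loss | 55.9% |

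**5. Detectable difference and interval.** On 4 df, 80% power needs a noncentrality of 3.76.
- At ICC 0.01: 3.76 × 2.873 = 10.8 points.
- At ICC 0, SE = 16 × √(2/77.4) = 2.57, giving 9.7 points. At ICC 0.05, the design effect is 1 + 24.8 × 0.05 = 2.24 and the SE 3.85, giving 14.5 points.
- 95% half-width at ICC 0.01: 2.776 × 2.873 = 7.98 using the true SE. Because an SE estimated on 4 df averages about 0.94 of the true one, the expected half-width is about 7.5. So the half-width is 7.5 to 8 points, roughly twice the 4-point relevant change; the full interval is about 15 to 16 points wide.

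**6. The planned test run at patient level.** A two-group t-test ignoring hospital understates the SE by √1.248 = 1.117. Its true two-sided alpha is the probability that |Z| exceeds 1.96/1.117 = 1.754, which is 7.9%. Simulation gave 8.0%, with 92% rejection at a 9-point difference.

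**The case against.** **The planned test is a patient-level t-test, so its own df apply, and its power is about 92%.** The arithmetic is right, but that test runs at about 8% alpha at the article's own ICC. Its rejection rate is not power at 0.05. As the analysis section stands, the more immediate consequence is excess false positives; the 65% becomes the trial's power once the analysis is made valid. That is why the two sections need changing together.

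**Another valid analysis could restore the 80%.** A mixed model with a random hospital effect has the same 4 between-hospital df for condition. Baseline adjustment may reduce the variance, and is already planned for the follow-up models, but the sample size rests on the SD of change and claims no such gain. The documents give no figure to quantify it.

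**Few suitable hospitals existed.** The Discussion says that only a minority of Dutch hospitals had a palliative care team. This is a good reason to keep six hospitals, but not to state 80%.

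**Stronger readings a reader might infer.**
- *The design-effect route itself falls a few patients short*, because it uses a cluster size of 64/3 rather than the larger number analysed. This holds only if 64 is accepted as the starting point. The stated 9 and 16 give 51, which with a self-consistent cluster size needs 60.8 analysed and 67.6 recruited per arm. The planned 86 exceeds that.
- *The 64 came from a larger SD.* No other SD appears in the article. A standardised difference of 0.5 fits 64, but nothing shows how it arose.
- *A non-significant result will be taken as proof of no effect.* The article says nothing of the kind.

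**Conclusion.** The power statement is wrong as written. At the article's stated difference, SD, ICC, number of hospitals and loss, a valid comparison of conditions has about 65% power instead of 80%. The shortfall does not depend on the ICC or on the loss: it remains at ICC 0 (74%) and with complete follow-up (69%).

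Nor does it depend on how the mismatch between 64 and 9/16 is resolved. If the working standardised difference was 0.5, for example 8/16, power is lower, about 56%.

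The conclusion assumes equal hospital sizes, roughly normal hospital means, an analysis of change without variance reduction from covariates, and 4 df for the condition effect. It concerns the stated power and the analysis that must go with it. It does not show that the number of patients is too small by the design-effect calculation alone.

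**What to change.** Keep six hospitals and 86 per arm, and make these changes.

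1. In Sample size calculation, replace the 80% with about 65% power for 9 points (SD 16, ICC 0.01, 10% loss, 4 df). Give the detectable difference of about 11 points, and the range over ICC 0 to 0.05: power 74% to 43%, detectable difference 9.7 to 14.5 points. Reconcile the 64 per group with the stated 9 and 16; if 8/16 was meant, the 4-df power is about 56%.
2. In Statistical analysis (intervention study), replace the primary t-test with an analysis that accounts for hospital: a t-test on hospital means, or a mixed model with a random hospital effect and small-sample df, in either case adjusted for baseline SGRQ.
3. State that the primary result is reported as an estimate with its 4-df 95% confidence interval, with an expected half-width of about 7.5 to 8 points.

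The cost is a less favourable power figure and wider intervals than the patient-level test would show. No further patients or hospitals are needed. Restoring 80% on 4 df at 9/16 would instead take about 43 completers per hospital, or about 48 enrolled after 10% loss.
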